#### Process Evaluation

A process evaluation will be carried out to gain insight into the factors influencing the effectiveness of the intervention program of Mindful VIP, such as the organisational context, receipt and implementation of the program.

#### Economic Evaluation

The economic evaluation aims to determine the cost-effectiveness of the intervention compared to the usual care from the societal and employer's perspective. Also, the cost-benefit analysis will be performed from the employer's perspective. The time horizon will be one year, similar to the trial. Analyses will be performed according to the intention-to-treat principle. In the main analysis, missing data will be imputed using fully conditional specification [55]. Sensitivity analyses will be done to assess the robustness of the results.

First, the total societal and employer's costs will be estimated, and compared between the intervention and control group. The 95% confidence intervals will be estimated using approximate bootstrap confidence intervals [56]. Societal costs include all cost measures described in the method section. From the employer's perspective, only costs relevant to the company are included (i.e. intervention, referral, and productivity-related costs). For the cost-effectiveness analysis (CEA), incremental cost-effectiveness ratios will be calculated by dividing the difference in costs between both groups by the difference in effects on the primary outcome measures (societal perspective) and work-related outcomes measures (employer's perspective). Bootstrapped cost-effect pairs will be graphically presented on cost-effectiveness planes [57]. Cost acceptability curves will be generated, showing the probability for cost-effectiveness of the intervention at various ceiling ratios. Also, a cost-benefit analysis (CBA) will be performed in which the incremental intervention and referral costs will be compared to the incremental productivity-related costs.

### Sample Size Calculation

The sample size was based on finding an effect on work engagement, measured using the UWES [7]. The mean score for work engagement was 3.82 (sd = 1.1) on a scale from 0-6 [7]. An effect of a 10% increase in mean score was expected to be relevant and feasible. With a power of 90% and a two-sided alpha of 5%, both groups needed 175 workers. Accounting for a loss to follow-up of 25% over 12 months, each group needed 234 workers at baseline, thus an initial total of 468 workers for the two groups.

After recruiting 200 participants, the preliminary baseline characteristics were examined. It appeared that within our study population the standard deviation was smaller than the value reported in literature (0.83). With this knowledge, the power was recalculated, leading to a group size of 89 participants. When taking into account a 25% loss to follow-up, both groups needed 119 workers, thus a total of 238 workers to be included at baseline.

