**Weight status**		
BMI, kg/m^2^, *m *± *sd*	24.74 ± 3.96	24.66 ± 3.56
Underweight (≤ 18.49 kg/m^2^), *%*	0.80	0.00
Normal weight (18.50-24.99 kg/m^2^), *%*	63.40	59.40
Overweight (25.00-29.99 kg/m^2^), *%*	25.60	32.00
Obese (≥ 30.00 kg/m^2^), *%*	9.40	8.60
Waist circumference (cm), *m *± *sd*		
Men	91.44 ± 10.72	91.39 ± 8.67
Women	80.30 ± 10.46	80.41 ± 9.29

* Higher vocational education or university ** Measured by the UWES 17 (Schaufeli & Bakker, 2003)

The mean score for work engagement was 4.09 in the intervention group and 4.02 in the control group (Table 5). Furthermore, of all the participants, 60.1% did not engage in vigorous physical activity in leisure time at all; 0.4% was underweight (< 18.50 kg/m^2^), about 29% was overweight (BMI between 25 kg/m^2 ^and 30 kg/m^2^), and about 9% was obese (BMI > 30 kg/m^2^).

No differences were observed between the intervention and control group for any of the variables, except for vigorous physical activity (p = .002).

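### The recalculated 89 per group does not follow from the smaller SD alone; the target difference apparently rose from 0.382 to about 0.405 without being stated

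*Protocol article*

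**What the plan says.** All the planning figures are in the section Sample Size Calculation of the protocol article. The reference values come from the literature: "The mean score for work engagement was 3.82 (sd = 1.1) on a scale from 0-6". The target is given in relative terms: "An effect of a 10% increase in mean score was expected to be relevant and feasible". The first result follows: "With a power of 90% and a two-sided alpha of 5%, both groups needed 175 workers". Allowing for 25% loss, this becomes 234 per group and 468 in total.

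The second paragraph of the section revises this. "After recruiting 200 participants, the preliminary baseline characteristics were examined", and the SD turned out to be 0.83 rather than 1.1. No other revised value is given. The text then says: "With this knowledge, the power was recalculated, leading to a group size of 89 participants". With 25% loss this becomes 119 per group and 238 in total.

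The section Baseline Characteristics reports that 257 were randomised (129 and 128). Table 5 gives baseline work engagement of 4.09 (SD 0.81) in the intervention group and 4.02 (SD 0.91) in the control group.

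**The concern.** The recalculation is presented as a consequence of the smaller SD. Anyone who repeats it with the mean, percentage, alpha and power printed in the same section gets a larger number than the article does. So either the result is wrong for those inputs, or another input changed and was not reported.

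This matters because the figure justifies the final size of the trial for its primary endpoint. A reader of a null result needs to know whether 90% power was planned for a difference of 0.382 or of about 0.405 UWES points. The text does not say.

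**Working it through.** **Inputs.** From Sample Size Calculation: mean 3.82, SD 1.1 and later 0.83, 10% increase, two-sided 5%, 90% power, 25% loss. From Baseline Characteristics and Table 5: 129 and 128 randomised, means 4.09 and 4.02, SDs 0.81 and 0.91.

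**Formula.** Normal approximation for two means with equal groups: n per group = 2 × (1.960 + 1.2816)² × SD² / d², rounded up. Here 2 × (1.960 + 1.2816)² = 21.015. Loss is handled as n / 0.75, rounded up.

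**1. First calculation.** d = 0.10 × 3.82 = 0.382, SD 1.1.
- n = 21.015 × 1.21 / 0.1459 = 174.3, so 175.
- 175 / 0.75 = 233.3, so 234; total 468.

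All three figures match the article. This confirms the formula, a target of 0.382 in that calculation, and that no credit was taken for baseline adjustment.

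**2. Recalculation, changing only the SD.** d = 0.382, SD 0.83.
- n = 21.015 × 0.6889 / 0.1459 = 99.2, so 100.
- 100 / 0.75 = 133.3, so 134; total 268.

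The article gives 89, 119 and 238. The loss step itself is right (89 / 0.75 = 118.7, so 119); the difference lies in the 89.

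**3. Power at 89 per group for 0.382.**
- Standard error = 0.83 × √(2/89) = 0.1244.
- 0.382 / 0.1244 − 1.960 = 1.11, so power is 86.7% (86.3% with the t distribution).

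**4. Other settings.** With d = 0.382 and SD 0.83, one-sided testing gives 81, 85% power gives 85, 80% power gives 75, and the t-based calculation gives 100.2. None gives 89. Keeping d = 0.382, an SD of about 0.785 would be needed.

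**5. The 10% applied to the study population's own mean.**
- Weighted mean in Table 5 = (129 × 4.09 + 128 × 4.02) / 257 = 4.055, so d = 0.4055.
- n = 21.015 × 0.6889 / 0.1644 = 88.0, rounded up to 89; then 119 and 238.
- Power at 89 for 0.4055 is 90.3%.

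Means of 4.04 to 4.055 give exactly 89. The two arm means taken singly give 90 (at 4.02) and 87 (at 4.09).

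**6. How much of the cut each change explains.** The SD alone takes the total from 468 to 268, a fall of 200. The larger difference takes it from 268 to 238, a further 30. So 30 of the 230 come from the unstated change.

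**7. The trial as randomised.** 257 × 0.75 / 2 = 96.4, taken as 96 per group. The pooled SD from Table 5 is √((128 × 0.81² + 127 × 0.91²) / 255) = 0.861.

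| Difference | SD | Power at 96 per group |
|---|---|---|
| 0.382 | 0.83 | 89.0% |
| 0.382 | 0.861 | 86.7% |
| 0.4055 | 0.861 | 90.4% |

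**8. Baseline adjustment.** The planned analysis of covariance multiplies the residual variance by 1 − r², where r is the correlation of baseline with follow-up. The article gives no r. A value of about 0.32 would by itself reduce 99.2 to 89. Assuming r between 0.5 and 0.7, power for 0.382 with 96 per group and SD 0.861 is about 94% to 99%.

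**The case against.** The strongest reply is that 89 is not an error. The value 0.382 is printed nowhere; the criterion is a 10% increase in the mean. The recalculation followed a look at baseline characteristics in the plural, so the mean and the SD may well have been updated together, with only the SD reported. On that reading 89 is what the formula gives, and 90% power is correct for the difference used.

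Much of this stands. A reader might infer that 89 is a miscalculation and that the 90% claim is simply false. The documents do not support that, because step 5 reproduces 89, 119 and 238 exactly. A reader might also infer that the target was raised to halve the trial. The figures do not support that either, since the smaller SD explains most of the reduction. Nor do the SDs in Table 5 make the SD of 0.83 wrong: the recalculation used what was known after 200 recruits, and the final values came later.

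What does not stand is that the paragraph is adequate as written. The section states one mean and one changed input, and together they give 100. The mean of the first 200 is not reported, so the reader cannot confirm the benign explanation. If it is right, the target in UWES points rose by about 6% (0.4055 / 0.382 = 1.06) without being mentioned.

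**Conclusion.** The point holds as a minor correction to a stated figure. On the inputs printed in Sample Size Calculation, an SD of 0.83 requires 100 per group, 134 after loss and 268 in total, and 89 per group gives about 87% power for 0.382. The likeliest explanation is an unstated rise in the target from 0.382 to about 0.405. That rests on the final-sample mean of 4.055 being close to the unreported mean of the first 200 participants.

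The consequence is small. The 257 randomised exceed the stated 238 and fall 11 short of 268. With 25% loss, power for 0.382 is about 89% at SD 0.83, one point below the nominal level, and the planned baseline adjustment would probably more than make this up. It gives no reason to doubt the design, or to enrol more.

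**What to change.** Correct the second paragraph of Sample Size Calculation in one of two ways:

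- State that the target became 10% of the mean observed in the first 200 participants, give that mean and the resulting difference (about 0.405 points), say why that difference is the relevant one, and make clear that the 90% power applies to it.
- Or keep 0.382 as the target and report 100 per group, 134 after loss and 268 in total.

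In either case add the power of the 257 randomised, with 25% loss (about 96 per group), for 0.382: about 89% at SD 0.83. As an optional update, give the values at the final pooled SD of 0.86: about 87% for 0.382 and about 90% for 0.405. If power under the analysis of covariance is also quoted, state the assumed correlation beside it.

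The cost is a few sentences. If 0.382 is kept, the stated power becomes slightly less favourable. Enrolment, design and analysis do not change.

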### Baseline Characteristics

Informed consent was obtained from 260 participants, of whom 258 participated in the baseline measurement of BMI and waist circumference. The questionnaire was completed by 257 eligible participants, who were subsequently randomly assigned to either the control or intervention group. The intervention group had 129 participants, and the control group had 128 participants.

Table 5 summarizes the baseline characteristics for the intervention and control group. Demographic characteristics as presented in Table 5 show that the majority of the study population was female (67.3%). Most of the participants were married or had a significant other (77.4%). More than four out of five participants were highly educated (completed higher vocational education or university).

**Table 5 T5:** Baseline characteristics

	Intervention group (n = 129)	Control group (n = 128)
**Demographics**		
Gender, Female *%*	63.56	71.09
Marital status: Married or significant other, %	81.39	73.43
Education: Highly educated*, *%*	76.74	85.93
Age, years, *m ± sd*	46.0 *± *9.4	45.1 *± *9.6
**Prognostic factor**		
Need for cognition, *m ± sd*	3.67 *± *0.51	3.75 *± *0.59
**Work engagement**		
Work engagement **, *m *± *sd*	4.09 *± *0.81	4.02 *± *0.91
Vigor, *m *± *sd*	4.23 *± *0.83	4.11 *± *0.91
Dedication, *m *± *sd*	4.39 *± *0.91	4.26 *± *0.96
Absorption, *m *± *sd*	3.77 *± *0.91	3.82 *± *0.91
**Energy Balance Related behaviours**		
Vigorous physical activity in leisure time, minutes per week, *m *± *sd*	86.32 *± *158.93	51.05 *± *127.45
Not engaging in vigorous activity in leisure time, *%*	50.40%	69.50%
Sedentary behaviour at work, minutes per working day, *m *± *sd*	496.74 ± 136.67	490.19 *± *113.96
Daily fruit intake in pieces, *m *± *sd*	1.51 *± *0.95	1.44 *± *0.93
Daily vegetable intake in grams, *m *± *sd*	183.55 *± *74.00	182.43 *± *83.36
**Weight status**		
BMI, kg/m^2^, *m *± *sd*	24.74 ± 3.96	24.66 ± 3.56
Underweight (≤ 18.49 kg/m^2^), *%*	0.80	0.00
Normal weight (18.50-24.99 kg/m^2^), *%*	63.40	59.40
Overweight (25.00-29.99 kg/m^2^), *%*	25.60	32.00
Obese (≥ 30.00 kg/m^2^), *%*	9.40	8.60
Waist circumference (cm), *m *± *sd*		
Men	91.44 ± 10.72	91.39 ± 8.67
Women	80.30 ± 10.46	80.41 ± 9.29

* Higher vocational education or university ** Measured by the UWES 17 (Schaufeli & Bakker, 2003)

The mean score for work engagement was 4.09 in the intervention group and 4.02 in the control group (Table 5). Furthermore, of all the participants, 60.1% did not engage in vigorous physical activity in leisure time at all; 0.4% was underweight (< 18.50 kg/m^2^), about 29% was overweight (BMI between 25 kg/m^2 ^and 30 kg/m^2^), and about 9% was obese (BMI > 30 kg/m^2^).

No differences were observed between the intervention and control group for any of the variables, except for vigorous physical activity (p = .002).

## Discussion

In this paper, the development of the Mindful VIP study, the design of its evaluation, and the baseline characteristics of the study population are described. The systematic development of the Mindful VIP program was based on the IM protocol, involving the target population and other stakeholders such as the management. This resulted in a program with the objective to increase work engagement, vigorous physical activity in leisure time, daily fruit and vegetable intake, and to decrease sedentary behaviour at work and during lunch time. Key resources of work engagement and key determinants of EBRB were explored for the target population. The chosen methods and strategies in the Mindful VIP program target these key resources and determinants. The program consists of an in-company mindfulness training, e-coaching, fruit and snack vegetables, a buddy system, and lunch walking routes.

The demographic characteristics related to the entire working population at the research institutes rather well in terms of age. The mean age of workers at the largest of the two research institutes was about 46 in 2010. The distribution of gender within the study population, however, differed from the entire working population at the two institutes in 2010. In our study population, there were more women (about 67%) than men, whereas in the actual working population, there are almost as many men (52%) as women. When interpreting the evaluation of the effects, this should be considered as it might have implications for the generalisability. In the process evaluation, the reach and recruitment of the target population will be further examined.

Baseline findings confirmed the findings and assumptions resulting from the needs assessment. Consistent with findings in the needs assessment and with findings in the Dutch population [7], the mean score for work engagement at baseline was average (according to scores defined by Schaufeli & Bakker [7]). Therefore, aiming at an increase in work engagement is considered feasible, as well as relevant. An increase in vigorous physical activity in leisure time, and a decrease in sedentary behaviour at work, are also feasible and relevant. Especially relevant would be to decrease the number of people not engaging in vigorous physical activity at all. The mean number of minutes per week engaging in vigorous physical activity and its non-normal distribution is comparable to a certain degree to findings in previous research [43] (mean = 70, sd = 168). Workers involved in the needs assessment indicated that they thought body weight was less important than mental health and well-being. The percentage of overweight and obese workers in the study population, 29% and 9%, respectively, was consistent with the Dutch working population, which is 31% overweight and 6% obese [58]. This is remarkable, however, since according to the same study, the prevalence of overweight and obesity among Dutch workers with scientific professions is significantly lower than the Dutch overall prevalence, namely 25.7% and 4.2%, respectively. Not all workers at the research institutes and included in this study perform scientific work, which may explain this discrepancy.

When making the choice for mindfulness training as a strategy of self-regulation, the need for cognition was assumed to be high. This was indeed the case, as the study population's need for cognition was relatively high (3.67-3.75 on a scale from 1 to 5).

Because the baseline characteristics were congruent with the findings in the needs assessment and the expectations on which the intervention was developed, we concluded that the systematic development based on the IM protocol produced a potentially appropriate intervention program, meeting the needs of this target population.

Furthermore, the baseline characteristics show that the intervention and control group did not differ significantly. Therefore, we concluded that randomization was successful, although for vigorous physical activity the groups did differ at baseline and this should be kept in mind when evaluating the effects.

### Strengths and Limitations

The first strength of the Mindful VIP study is targeting two threats to worker's health in the Western society: mental health problems and overweight as a result of a disturbed energy balance. A second strength of this study is that by developing the intervention in a systematic way, based on the IM protocol, the intervention is theory-based and the target population was involved in the development as well. As a result, the intervention is likely to be adequate to meet the needs of the target population, hopefully resulting in good compliance. Discussing the constraints of the implementation of the program and compliance with the target population decreases the likelihood of barriers in adoption of the program. Furthermore, the effectiveness will be evaluated in a two-armed RCT with two follow up measurements up to one year. Another strength of the study is that anthropometric measurements are conducted objectively, and physical activity and sedentary behaviour data are collected using a combination of subjective and objective methods.

This study also has limitations. As the intervention was developed for and by the target population, it is possible that this intervention is only suitable for the present study population. This means that the external validity might be limited. However, we feel that the intervention and study's results might be applicable to many other highly educated office workers as well. The two research institutes are comparable to the extent that they both conduct policy-based research, and mainly include office workers who perform mentally demanding work.

Another limitation of the study design is that blinding participants is not possible. On the one hand, the likelihood of a spill-over effect (i.e. contamination) is expected to be negligible, because the training and e-coaching only is accessible for those in the intervention group. On the other hand, all workers, for example, might take fruit when informed by colleagues from the intervention group. When evaluating the effects, this should be considered.

Further, the intervention only aims at the individual worker. Ideally, a combination of individual and environmental changes was included. A meta-analysis of the effects of worksite physical activity and dietary interventions have namely shown greater effects on weight related outcomes for combined interventions compared to interventions based on one component (i.e. either individual or environmental changes) [59]. Nevertheless, because of the randomisation at individual level, possibilities to achieve and evaluate environmental changes within the Mindful VIP study were limited. Within these limitations, however, some environmental changes have been made on a social level, generating support in the group training, and in the physical environment by providing fruit. Concerning work engagement, on the other hand, it has been hypothesized that changes in environmental resources only yield short term effects because workers tend to quickly accommodate changes, which they have not initiated themselves based on their personal resources [34]. Therefore, it would be more beneficial to aim principally at the personal resources of work engagement and the individually based intervention targeting work engagement in the present study thus meets that hypothesis. However, this raises the question of whether the responsibility to be engaged or feel well at work can entirely be abdicated on the worker, especially since it is work-related--thus there is a need for further research.

## Conclusion

The Mindful VIP program was developed to improve the work engagement and EBRB of workers performing mentally demanding, sedentary work. The results of the needs assessment during the systematic development of the intervention were consistent with the findings at baseline measurement. It is therefore likely that this program fits the target population well, increasing the likelihood of compliance and effectiveness. To determine the (cost-) effectiveness of this program, a RCT will be conducted. Related outcomes such as mental health, vitality, BMI, general health perception, need for recovery and work-related outcomes will also be examined. Results of the RCT will be available in 2012.
